# Increasing return-to-work among people on sick leave due to common mental disorders: design of a cluster-randomized controlled trial of a problem-solving intervention versus care-as-usual conducted in the Swedish primary health care system (PROSA)

**DOI:** 10.1186/s12889-018-5816-8

**Published:** 2018-07-18

**Keywords:** Common mental disorders, Adjustment disorders, Anxiety disorders, Depression, Cluster-randomized trial, Problem solving skills, Return to work, Sick leave, Economic evaluation, Ethical evaluation

## Abstract

**Background:**

Common mental disorders affect about one-third of the European working-age population and are one of the leading causes of sick leave in Sweden and other OECD countries. Besides the individual suffering, the costs for society are high. This paper describes the design of a study to evaluate a work-related, problem-solving intervention provided at primary health care centers for employees on sick leave due to common mental disorders.

**Methods:**

The study has a two-armed cluster randomized design in which the participating rehabilitation coordinators are randomized into delivering the intervention or providing care-as-usual. Employees on sick leave due to common mental disorders will be recruited by an independent research assistant. The intervention aims to improve the employee’s return-to-work process by identifying problems perceived as hindering return-to-work and finding solutions. The rehabilitation coordinator facilitates a participatory approach, in which the employee and the employer together identify obstacles and solutions in relation to the work situation. The primary outcome is total number of sick leave days during the 18-month follow-up after inclusion. A long-term follow-up at 36 months is planned. Secondary outcomes are short-term sick leave (min. 2 weeks and max. 12 weeks), psychological symptoms, work ability, presenteeism and health related quality of life assessed at baseline, 6 and 12-month follow-up. Intervention fidelity, reach, dose delivered and dose received will be examined in a process evaluation. An economic evaluation will put health-related quality of life and sick leave in relation to costs from the perspectives of society and health care services. A parallel ethical evaluation will focus on the interventions consequences for patient autonomy, privacy, equality, fairness and professional ethos and integrity.

**Discussion:**

The study is a pragmatic trial which will include analyses of the intervention’s effectiveness, and a process evaluation in primary health care settings. Methodological strengths and challenges are discussed, such as the risk of selection bias, contamination and detection bias. If the intervention shows promising results for return-to-work, the prospects are good for implementing the intervention in routine primary health care.

**Trial registration:**

ClinicalTrials.gov Identifier: NCT03346395 Registered January, 12 2018.

## Background

It is estimated that common mental disorders (CMDs), i.e. mild to moderate depression, anxiety, adjustment and stress-related disorders affect about one-third of the European working-age population. In Sweden, after a reduction in sickness absence due to CMDs between 2005 and 2010, sickness absence started to increase again in 2011. At present, CMDs are the most common cause of sick leave in Sweden. In January 2016, CMDs were the cause of about 45% of all sick leave among women and 32% of all sick leave among men [1]. Besides the individual suffering, with its negative impact on the individual’s well-being, financial circumstances, social network and risk of stigmatization, the cost for society in terms of health care, sick leave and productivity loss for employers is high. In 2013, the total costs for mental health in Sweden, including sick leave, amounted to some SEK 65 billion (approx. EUR 6 billion) [2].

The first choice of clinical treatment for CMDs is psychological treatment, primarily cognitive behavioral therapy and/or medication [3]. These treatments have positive effects on symptom reduction and improved functioning, yet symptom reduction is not accompanied by increased return-to-work (RTW) [4, 5]. Previous research shows that, to increase RTW among persons on sick leave due to CMDs, work place interventions which include cooperation between the person on sick leave, his/her employer, the health care services, the social insurance agency and the occupational health services are needed [6–8]. Cooperation between the stakeholders (i.e. health care services, employers, social insurance agency, and occupational health services) is a prerequisite for reducing sick leave and increasing RTW. However, a major problem is the lack of cooperation between these stakeholders. Moreover, primary health care often fails to focus on RTW and workplace related interventions [9, 10].

In line with previous research, we found that the first concern of primary health care professionals is patients’ psychological and physical well-being; the process of RTW is often of secondary importance [10]. On the basis of previous evaluations of an evidence-based intervention (i.e. interventions based on problem-solving therapy), we know that this type of intervention has promising effects on sick leave among persons with CMDs [7, 11]. However, the Swedish primary health care system has a limited history of workplace interventions which include cooperation with the workplace. This represents a new challenge for primary health care.

Workplace interventions are defined as interventions which target or involve the workplace, work organization, work conditions or work environment and/or occupational (case) management strategies with active stakeholder involvement [12]. Evidence of effective workplace RTW interventions for people with CMDs is limited and the studies vary with respect to inclusion criteria (cf. [13, 14]). However, it has been shown that interventions with a workplace component, including vocational counseling, are more likely to succeed in increasing RTW than interventions that do not include such a component (cf. [6, 15, 16]). The British National Institute of Clinical Excellence’s guideline on long-term sickness absence and work incapacity identifies early, multidisciplinary and workplace-focused interventions as those most likely to give positive results [17]. In a recent review, no significant benefits were found for coordinated RTW programs [13]. However, only two of the review’s 14 studies reported outcomes for populations with CMDs and these were conducted outside Sweden, in coutries with other social security systems than the Swedish system [13]. A key element of workplace interventions is cooperation between the employer, the person on sick leave and health care professionals. The cooperation between these actors in the RTW process has been described as challenging because each actor represents different perspectives and interests [9].

Previous studies have shown that problem-solving skills and work-focused cognitive behavioral therapy are more effective than guideline-based interventions in reducing the time to first RTW among employees on sick-leave for CMDs. Guideline-based interventions did not reduce time to return to full-time work [7, 14, 18, 19]. In a web-based intervention which included problem-solving skills and relapse prevention, a significantly faster first RTW was found for the intervention group. No significant differences were found for time until full RTW or in reduced total number of days on sick leave at the 12-month follow-up [20]. A review of interventions to improve time to first RTW among people with depression gave moderately good evidence that workplace interventions in combination with clinical interventions reduced the number of days on sick leave significantly more than clinical interventions alone [21]. Similar results were found by an updated review which evaluated the effects of workplace interventions among workers with mental health problems. The results demonstrated a significantly better reduction in time to first RTW than care-as-usual [15]. A cluster-randomized controlled trial in the Netherlands demonstrated the 12-month effectiveness of a problem-solving intervention for reducing recurrent sick leave among workers with CMDs. The intervention group had a lower incidence of recurrent sick leave than the control group which received care-as-usual [11]. Economic evaluations of such interventions have shown varying results, from reduced to increased health care costs [22–25].

To date, only a limited number of studies have evaluated the effectiveness of interventions to improve RTW in a primary health care population [6, 7, 15]. There is thus a need for more RTW research in the primary health care context. Previous studies of problem-solving interventions have been conducted in countries with work environments, sickness absence and social security systems which differ from those in Sweden [6, 7, 11, 15]. The (financial) implications of employers to cooperating with the health care services may also differ in the Swedish system. These differences may in turn affect the effective components of the intervention and influence the way the intervention works and how likely it is to result in successful outcomes. Most studies have primarily focused on time to first RTW [6, 15] or recurrent sick leave after RTW [7]. The effect evaluations have been conducted in occupational health service settings, have had relatively small sample sizes and lacked a long-term follow up (i.e. ˃ 12 months) [8]. In Sweden, the primary health care service is responsible for treatment, issuing sickness certificates and assessing the individual’s work capacity. Hence, it is important to adapt the problem-solving intervention to the primary health care setting and evaluate the intervention in that context.

This paper presents the design of a study, which evaluates a work-related problem-solving intervention provided at primary health care centers (PCCs) for employees on sick leave due to common mental disorders. We hypothesize that participants who have undergone the problem-solving intervention will have fewer total sick leave days and fewer recurrent sick leave periods after RTW than the participants who receive care-as-usual (CAU). In addition, a process evaluation of the intervention and its association with the effects on sick leave, an economic evaluation and an evaluation of the ethical issues raised by the intervention will be conducted.

## Methods

The CONSORT statement and the extension for randomized controlled trials were used to describe the study design [26, 27].

### Study design and setting

The study is designed as a two-armed cluster-randomized controlled trial of a problem-solving intervention to reduce sick leave compared with CAU (Fig. 1). In Sweden, persons who cannot work due to disease or injury are entitled to benefits from a mainly tax-funded social insurance system. Individuals who are gainfully employed receive economic compensation from their employer for the first 14 days (except for one qualification day). Thereafter, the Social Insurance Agency grants the benefits. A sickness certificate issued by a physician in the primary health care system is needed from day 8. In an effort to improve RTW, Swedish county councils have introduced rehabilitation coordinators (RCs) whose role is to coordinate the RTW of persons who are on sick leave for whatever reason. RCs are commonly registered nurses, physiotherapists, occupational therapists or social workers.

**Fig. 1 Fig1:**
[figure not shown]
Flowchart and overview of the trial

The study will be conducted in the primary health care service of the Västra Götaland region of Sweden. This service comprises some 200 publicly-funded PCCs which provide health care for 1.6 million people of all ages. Around 180 (90%) of the 200 PCCs have an on-site RC.

### Recruitment of rehabilitation coordinators

RCs were recruited from PCCs in the Västra Götaland region. Information about the study was sent to managers in the region by the first author ([name]) and was given at meetings with PCC managers and RCs. Only RCs not participating in other ongoing interventional studies at the time of inclusion were invited to participate. RCs were also excluded if they had an upcoming leave of absence (for example pregnancy leave, a sabbatical) or if they were leaving the PCC or retiring. About 80 coordinators received an invitation. Written information about the study was provided as well as a registration form and informed consent. Written informed consent was obtained from all RCs. The recruitment process resulted in 19 RCs covering 24 PCCs.

### Recruitment of participants

To be eligible for the study an employee must be on sick leave due to CMDs and must have been diagnosed by a physician at a PCC which is participating in the study. The current sick leave period should last a minimum of 2 weeks and a maximum of 12 weeks. Employees on sick leave will be recruited by a research assistant who screens medical records for inclusion and exclusion criteria. The research assistant will be blinded to group assignment. Employees who meet the inclusion criteria will be invited to join the study by the research assistant by email. Eligible employees will receive written information about the study. Those employees willing to participate must give written consent. They will then be sent the baseline questionnaire by email.

### Eligibility criteria

#### Inclusion criteria

Eligible participants can be included if they meet the following criteria:Employed women and men aged 18–59 yearsOn sick leave (i.e. a minimum of 2 weeks and a maximum of 12 weeks) with mild to moderate depression, anxiety or adjustment disorder (F 32, F 41, F 43) as the primary reason for sick leave, diagnosed by a physician according to the Swedish version of international statistical classification of diseases and related health problems - tenth revisionPhysician works at a PCC in the Västra Götaland regionAccept the employer’s involvementUnderstand written and spoken Swedish.

All eligible participants who meet the criteria and consent to participation will be included.

#### Exclusion criteria

Employees with severe depression; other severe mental disorders (i.e. psychotic or bipolar disorders or who have been referred to a psychiatrist); pregnancy; somatic complaints or disorders that affect work ability; those unable to read, write and understand Swedish will be excluded.

### Intervention

#### Training of rehabilitation coordinators in the intervention group

The RCs will take part in a two-day training course about the problem-solving intervention [28]. The training is provided by a licensed psychologist with extensive experience of problem-solving therapy and of supervising primary health care professionals. The RCs will complete a questionnaire about the quality of the training course and their problem-solving skills before and after the course, as a part of the process evaluation. The RCs will have support from a manual and three work sheets developed by the research group, all based on research into CMDs, the problem-solving intervention and the coordinator function. During the intervention period the RCs will receive supervision and feedback from the project leader whenever needed.

#### The problem-solving intervention

The intervention focuses on the individual and the involvement of the workplace [11, 29] in addition to CAU [3]. The added value on top of CAU is the intervention’s problem-solving process and the coordination by the RC between the employee on sick leave, his/her employer and the health care professionals.

Communication between the employee, the RC and the employer is needed for making an inventory of problems, opportunities and identifying the help needed to solve the problems [11]. The present intervention is a modified version of the Dutch sharp-at-work intervention [29] which aimed to prevent recurrence of sick leave among employees with CMDs who had returned to work. The Dutch target group differed from the target group of the present study, i.e. persons on sick leave. The new, adapted intervention is a five-step problem-solving process which aims to identify and find possible solutions to problems perceived as obstructing the RTW process (Fig. 2). A meeting with the person on sick leave, his/her employer and the RC is included in the process, as previous research has stressed the importance of communication between the different stakeholders [30]. The intervention comprises the following five steps:Making an inventory of problems and/or opportunities related to RTW; a collaborative approach involving employee and RC; employer and RC.Brainstorming about solutions, involving employee and RC.Writing down solutions, identifying the support needed to implement them and assessing their applicability, involving employee and RC.A meeting with the person on sick leave, the employer and the RC to discuss solutions and make an action plan, involving employee, RC and employer.Evaluation of the action plan and implementation of solutions, involving employee and RC.

**Fig. 2 Fig2:**
[figure not shown]
Overview of the problem solving intervention

The work-focused problem-solving intervention starts with the RC interviewing the employee who is on sick leave. The RC facilitates the employee’s participation in his/her RTW-process by supporting and encouraging the employee to take active part in brainstorming and prioritizing obstacles and possible solutions for RTW. The first consultation between the employee and the RC lasts about 45 min and is summarized in the form of a preliminary list of identified problems and possible solutions. Thereafter the RC interviews the employer by telephone about problem orientation, e.g. how aware the employer is of the employee’s health problems; how these problems are apparent in the workplace; the employer’s understanding of the causes of the illness. This takes approximately 15 min. The next step is a meeting of 45–60 min between the employee, the employer and the RC. In the problem-solving process, the RC facilitates a dialogue between the employee and the employer; thus the employee and employer are responsible for identifying obstacles and facilitators related to RTW. They also identify and prioritize solutions and make an action plan. The action plan also addresses relapse prevention. The RC evaluates the action plan with the employee.

### Care as usual (CAU)

The RCs in the control condition will continue to deliver CAU during the study period. CAU may include strategies for the RTW process and may involve the employer. However, the strategies used by the RCs to date are not structured in the same way as in the intervention condition, and do not follow an explicitly stated guidance by problem-solving therapy.

CAU involves cognitive behavioral therapy or medical treatment, or a combination of both [3], as well as the coordination of RTW (meeting with a RC). We will make no specific attempts to ensure that the physicians follow the guidelines for the treatment of CMDs [3]. The participants, their physicians and, if relevant, their psychologists, will not receive any information from the project group about the problem-solving intervention.

### Measurements and procedure

Data will be collected by questionnaires, text messages and the use of registers. Register data will be collected from the Micro Data for the Analysis of Social Insurance register (MiDAS) from the Social Insurance Agency, the Västra Götaland region’s Vega register which is the patient register for Region Västra Götaland, and the Longitudinal Integration Database for Health Insurance and Labor Market Studies (LISA), administrated by Statistics Sweden. Web-based questionnaires will be administered at baseline and after 6 and 12 months. Text messages will also be sent to the employees every fourth week over a 12-month period. The use of text messages enables us to measure short-term sick leave (≤ 14 days) that is not covered by the MiDAS register. A 36-month follow-up of sickness absenteeism based on register data is planned.

### Primary outcome

#### Registered sick leave

The primary outcome is the total number of days of sick leave 18 months after baseline. Data from MiDAS will be collected from baseline until the 18-month follow-up and for the 24 months before baseline. Information about the number of days on sick leave, episodes of sick leave after RTW, and receipt of disability pension will be collected for all participants. Sickness benefit and disability pension will be analyzed separately.

The total number of days of registered sick leave will be calculated after 36 months in the same way as at the 18-month follow-up.

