### Methodological considerations

The cluster-randomization, in which the RCs are randomized to intervention and control groups, reduces the risk of contaminating the employees who participate in the study. The RCs will only provide the problem-solving intervention or CAU. Another strength of the study is that participants will be selected by a project assistant who screens medical records for eligible employees on sick leave. The project assistant will have no previous knowledge about the participants or the randomization, thereby reducing the risk of selection bias.

In the Swedish social insurance system, the employer usually pays for sick leave up to and including day 14. The MiDAS register therefore contains sick leave data from day 15 of sick leave. Since short-term sick leave may predict future long-term sick leave, valuable information about short-term sick leave will be collected from the employees. However, with self-reported questionnaires there is always a risk of recall bias and drop-out. The use of text messages facilitates repeated measurements with short recall periods, while the questionnaires are administered at baseline and at 6 and 12-month follow-up. The 6 and 12-month follow-ups may increase the risk of recall bias, but this risk has to be weighed against the frequency of the questionnaires that the participants have to fill in.

The data collected in the process evaluation will be analyzed before the primary and secondary outcomes in the effectiveness evaluation are known to the research group, to prevent biasing interpretations of the intervention’s effectiveness. One of the strengths of the proposed method for the economic evaluation will be its use of comprehensive individual-level data collected for administrative purposes, on both direct and indirect costs. A strength of the proposed methodology for ethical analysis is it context-sensitivity in relation to the Swedish health care system and its inherent ethical values and norms. However, ethical analysis is, on top of demands for internal consistency, dependent upon being critically examined and acknowledged as relevant by the stakeholders. Hence, dialogue concerning this analysis is crucial.

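### The primary total of sick leave days comes from a register that starts at day 15 of a spell, so relapse days are under-counted and the arm difference shifts if relapse differs between arms

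*Protocol article*

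**What the plan says.** Under the heading Registered sick leave, the article defines the outcome: "The primary outcome is the total number of days of sick leave 18 months after baseline". The only source named there is the register: "Data from MiDAS will be collected from baseline until the 18-month follow-up and for the 24 months before baseline". The 36-month count is to be made the same way, and episodes of sick leave after return to work are also to be collected.

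Methodological considerations gives the register's coverage: "The MiDAS register therefore contains sick leave data from day 15 of sick leave". The stated reason is: "In the Swedish social insurance system, the employer usually pays for sick leave up to and including day 14". Measurements and procedure adds: "The use of text messages enables us to measure short-term sick leave (≤ 14 days) that is not covered by the MiDAS register". The text messages run every fourth week for 12 months. Self-reported short-term leave is listed under Secondary outcomes, and nothing says that it enters the primary total.

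On entry, Recruitment of participants says: "The current sick leave period should last a minimum of 2 weeks and a maximum of 12 weeks". On relapse, the Background hypothesises both a lower total and less recurrence after return to work. The description of the intervention says: "The action plan also addresses relapse prevention".

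**The concern.** The article treats the register gap as a matter of missing short absences. It does not say that a long new spell also loses its first 14 days, or that this affects the primary comparison.

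The index spell and later spells are thus scored differently. Participants enter during a spell of at least 2 weeks, so the unregistered start of that spell normally lies before baseline and its later days are counted. Equal time off work then scores lower when it is broken by a return and a relapse than when it is continuous.

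The trial itself expects recurrence to differ between arms. If the intervention prevents relapses, part of the saving is invisible in the primary outcome. If it produces earlier but less durable returns, the uncounted relapse days look like a benefit. In both cases a conclusion about total sick leave would rest on a count that omits some of it.

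**Working it through.** **Inputs from the article.** Source and window: MiDAS, baseline to 18 months. Register start: day 15 of a spell. Power: 110 per arm in 10 clusters of 11, intra-cluster correlation 0.010, alpha 0.05 (two-sided assumed), about 80% power for a 20% difference. The article gives no mean number of days, standard deviation, relapse rate or relapse length, so those are assumed below and varied.

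**1. One participant.** Registered days = index days after baseline + sum over new spells of max(L − 14, 0), where L is spell length. With 120 true days after baseline:

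| Pattern | Registered days | Under-count |
|---|---|---|
| one continuous spell | 120 | 0% |
| 60 + one relapse of 60 | 60 + 46 = 106 | 14/120 = 12% |
| 60 + two of 30 | 60 + 16 + 16 = 92 | 28/120 = 23% |
| 60 + three of 20 | 60 + 6 + 6 + 6 = 78 | 42/120 = 35% |

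**2. Arm difference.** Let D be the true difference (control minus intervention), r the mean number of new registered spells per person, and s the mean days per person in new spells of 14 days or less. Then

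observed difference = D − 14 × (r_control − r_intervention) − (s_control − s_intervention).

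If relapse is equal, both corrections vanish.

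**3. The plan's power figure.** Design effect = 1 + (11 − 1) × 0.010 = 1.10, so the effective size is 110/1.10 = 100 per arm. The 80% cannot be reproduced without a standard deviation. For a comparison of means it requires a standardised difference of (1.960 + 0.842) × √(2/100) = 0.396, that is, a coefficient of variation of 0.20/0.396 = 0.505. That value is used in step 4 only to express the shift as power.

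**4. Size of the shift.** Assume control means of 100, 150 and 200 days, a true 20% reduction, and short spells equal between arms.

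| New spells per person, control vs intervention | Observed difference (true 20 / 30 / 40) | Change | Power |
|---|---|---|---|
| 1.0 vs 1.0 | 20 / 30 / 40 | none | 80% |
| 1.0 vs 0.5 | 13 / 23 / 33 | −7 days (−35 / −23 / −18%) | 44 / 57 / 64% |
| 1.0 vs 1.5 | 27 / 37 / 47 | +7 days (+35 / +23 / +18%) | inflated |

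Example of the power figure: 13/50.5 × √(100/2) − 1.960 = −0.14, which gives 44%. With equal relapse the absolute difference is intact, but the relative one rises above 20%, to 20/86 = 23.3%, 30/136 = 22.1% and 40/186 = 21.5%.

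**5. Simulation with short spells included.** Assumed: exponential index remainder and relapse length (mean 40 days), relapse rate per year at work, 548 days of follow-up, 400,000 participants per scenario.

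| Scenario | True | Registered | Registered + 14 per new registered spell |
|---|---|---|---|
| A: index mean 120, rate 1.0 | 157.5 | 145.1 | 155.3 |
| B: index mean 120, rate 0.5 | 138.7 | 132.2 | 137.5 |
| C: index mean 100, rate 1.5 | 157.7 | 139.0 | 154.3 |

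- A vs B (fewer relapses only): true saving 18.8 days, registered 12.9 (31% lost), with add-back about 17.8.
- A vs C (nearly equal true totals, less durable return): registered 145.1 − 139.0 = 6.1 days of apparent benefit, with add-back 155.3 − 154.3 = 1.0.
- Separate runs of the A vs B contrast: with mean relapse 20 days, 10.0 true and 4.6 registered (54% lost); with 80 days, 30.6 and 24.9 (19% lost).
- Benefit through the index spell only (mean 120 to 96, rate 1.0 in both arms): 20.7 true and 21.4 registered. Little changes.

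**6. Text messages.** They cover 12 of 18 months, leaving 6/18 = 33% of the primary window without any record of spells of 14 days or less.

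**The case against.** The case for leaving the plan alone has weight. The outcome sits under a heading that calls it registered, the power statement also speaks of registered absence, and the article discloses the gap and collects short-term leave separately. An objective register count is a defensible primary outcome, and a sensitivity analysis could sit in an analysis plan that is not shown. This lowers the seriousness. It does not remove the point, because the abstract and the hypothesis speak of total days, and the article nowhere recognises the 14-day loss on long new spells.

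Several stronger readings are tempting but unsupported:

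- *The arm comparison is distorted whatever happens.* It is not. With equal relapse the absolute difference is unaffected, and a benefit that comes through a shorter index spell is registered almost exactly. The adapted intervention aims mainly at obstacles to returning to work; relapse prevention is one element of it.
- *Under-counts of 12% to 35% can be set against the 20% detectable difference.* They cannot. The former concern single participants and largely cancel when common to both arms.
- *A loss of about 31% is established.* It follows from an assumed 40-day relapse and no effect on index leave. The 6-day spurious benefit is also small beside sampling error: with a simulated standard deviation of about 114 days, the standard error is 114 × √(2/100), about 16 days.
- *The index spell is counted in full.* Only its days after baseline are, and the recruitment wording does not make certain that 14 days have passed by then.
- *The primary should be replaced by the register count plus a flat 14 days.* The employer's 14 days are qualified by the word usually, part-time leave complicates a flat addition, and a 14-day spell would score 0 while a 15-day spell scores 15.

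**Conclusion.** The point holds in conditional form. The primary count under-records days of new spells after return to work relative to days of the index spell. The absolute arm difference is consequently off by about 14 days times the arm difference in new registered spells per person, plus any difference in spells of 14 days or less. That is 7 days for each half-spell difference, before short spells. The direction is toward the null under the trial's own relapse hypothesis, in the intervention's favour if returns are earlier but less durable, and the effect is near zero if relapse is equal.

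The mechanism rests on the article's own statements. The percentages and power losses rest on assumed means, variation, relapse rates and relapse lengths, and the true size cannot be derived from the document. The stated sample size is not shown to be wrong. This is a cheap improvement, not a fatal flaw.

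**What to change.** 1. Describe the primary outcome wherever it appears as register-covered days, meaning day 15 onward of each spell.
2. Prespecify, at 18 and 36 months and identically in both arms, a key supporting analysis that adds up to 14 days for each registered spell that starts after baseline while the participant is employed. Exclude the index spell and any days before baseline, and state a rule for part-time leave.
3. Report new registered spells per person by arm beside the primary result.
4. State in advance that any claim about total sick leave will be limited if the two counts disagree.
5. Use the text-message days over the first 12 months as a further sensitivity analysis. The question asks for a number of days in four weeks, without dates, so these days cannot be cleanly assigned to spells outside the register. Comparing the text-message total by arm with the register counts for the same 12 months avoids double counting.

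Cost: an outcome derivation from MiDAS data and episodes already being collected, plus one extra table. The add-back remains an approximation because the employer only usually pays to day 14, and spells of 14 days or less stay uncovered after month 12.
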